## Abstract

**Background:**

The occurrence of postoperative cognitive deficits, especially after heart surgery, has been demonstrated in several studies. These deficits can clearly be noticed by the patients and by their close relatives in daily life. Furthermore, postoperative cognitive deficits can decrease quality of life in social functioning and earning capacity. The aim of this study is to investigate whether early postoperative cognitive training can reduce subjective and objective postoperative cognitive deficits.

**Methods:**

The proposed study is a multicenter, two-arm, randomized controlled trial involving 144 elderly patients undergoing elective heart-valve surgery with extracorporeal circulation. Patients will be assigned to either a training group or a control group. The intervention involves paper-and-pencil-based cognitive training, which is conducted for 36 min over a period of 18 days. The training starts about 1 week after surgery and is carried out during the hospitalized rehabilitation phase. The control group will not receive cognitive training or a placebo intervention. A detailed assessment of psychological functions and health-related quality of life prior to surgery at discharge from rehabilitation and 3 and 12 months after discharge will be performed. The primary outcome of this trial is the training effect on objective cognitive functions at discharge from rehabilitation. Secondary outcomes are the training effect on objective and subjective cognitive functions (3 and 12 months after discharge), depression, health-related quality of life, and the impact of perioperative cerebral ischemia on the training effect. Perioperative cerebral ischemia will be measured with postoperative magnetic resonance imaging including diffusion-weighted sequences.

**Discussion:**

Should it be shown that our cognitive training can improve postoperative cognitive deficits and quality of life, one possibility could be to integrate this intervention into early rehabilitation. Furthermore, we hope that the investigation of perioperative ischemia by diffusion-weighted magnetic resonance imaging will improve our understanding of neurobiological factors influencing the course of postoperative cognitive plasticity.

**Trial registration:**

German Clinical Trials Register (DRKS), DRKS00015512. Retrospectively registered on 21 September 2018.

## Background

Neurological complications of cardiac surgery include ischemic and hemorrhagic stroke, seizures, delirium, cerebral hyperperfusion syndrome, cranial and peripheral nerve injuries, and postoperative cognitive decline (POCD) [1]. Amongst these, POCD seems to have the highest incidence, but its frequency strongly depends on the inclusion/exclusion criteria, the follow-up interval and the diagnostic criteria used [2]. There is no uniform definition of POCD, but a widespread criterion for POCD is a decline of 1 standard deviation from preoperative to 3 months postoperative in at least two objectively measured cognitive functions such as verbal memory, attention, cognitive flexibility, language, or visuomotor abilities [2]. Three months after coronary artery bypass grafting (CABG) surgery, POCD occurs in 16% [3] to 23% [4] of patients, and POCD has even been reported in 31% of patients 3 years after undergoing CABG [4]. A longitudinal study assessing the incidence of POCD in CABG surgery reported early improvement in cognitive function within 6 months after surgery that was followed by a later decline and led to a 42% incidence of POCD after 5 years. In this study, early POCD could be identified as an important predictor of long-term cognitive decline [5]. Even though POCD often appears as subclinical, both patients and their relatives report a significant decrease in patients’ cognitive abilities in daily living up to at least 3 months after heart surgery [6]. In addition to POCD, postoperative cognitive improvement (POCI) is also reported, but its frequency seems to be 3–6 times lower than POCD [7].

Several perioperative conditions are discussed as potential pathophysiological mechanisms causing and promoting cerebral injury, such as global and regional hypoperfusion, pronounced temperature, arrhythmia, systemic inflammatory response, hemodilution, anesthesia itself and, particularly, cerebral (micro and macro) embolization followed by ischemia/reperfusion injury and subsequent blood-brain barrier dysfunction [8, 9]. A meta-analysis of randomized controlled trials has shown higher incidence of POCD in CABG with extracorporeal circulation (cardiopulmonary bypass, on-pump) compared to off-pump CABG 3 months after surgery [10]. In this respect, cerebral micro-embolization has been reported to substantially contribute to perioperative neurological complications [11].

Although the pathophysiology of POCD is still the subject of controversial debate, consequences of cognitive deficits are well-described. Aside from a decline in health-related quality of life (HQL) up to 5 years after surgery [12], POCD can result in reduced working and earning capacity with premature retirement, and diminished social functioning resulting in increased social dependency [13]. Cognitive abilities substantially contribute to personality and self-perception; in this light, daily perceived POCD can impose a profound and heavy burden on those concerned. For patients, relatives, and the healthcare system, it is of particular significance that POCD occurs during a highly vulnerable period of life, where cognitive deficits can quickly lead to loss of independence and thus increased need of long-term care [14].

Several studies have shown that patients with mild cognitive impairment (MCI) can benefit from computerized cognitive training [15]. These effects are mainly attributed to cognitive and neurological plasticity (i.e., the ability of the brain to alternate cognitive functions and structural or functional neurophysiological parameters through stimulation). In response to cognitive training, older healthy adults reproducibly present with an increased pattern in the gray and white matter structure [16]. Functional plasticity, on the other hand, shows a mixed pattern of increased and decreased activity in specific brain regions in older healthy adults and consistent increased activity in individuals with MCI, as a result of cognitive training [16]. Furthermore, a functional magnetic resonance imaging (MRI) study reported increased resting-state functional connectivity between the hippocampus and certain brain regions after effective cognitive training in patients with stroke [17]. Cognitive training is also associated with improvements in depression and everyday functioning [18]. To date, only one prospective investigation has addressed the value of cognitive training in patients undergoing cardiac surgery [19]. The authors reported a beneficial effect of memory and attentional training in patients who underwent CABG compared to patients who underwent CABG and received no additional cognitive training.

The purpose and primary outcome of this prospective, randomized and controlled study is to evaluate the effectiveness of a paper-and-pencil-based cognitive training program on objectively measured cognitive functions for patients undergoing cardiac surgery with extracorporeal circulation. The primary outcome will be evaluated directly after training at discharge from rehabilitation. The delivery of the cognitive training will start at the beginning of rehabilitation, which means approximately 1 week after surgery. Secondary outcomes are the training effect on cognitive functions, depression and health-related quality of life 3 and 12 months after discharge from rehabilitation, and the impact of perioperative cerebral ischemia on the training effect. Perioperative cerebral ischemia will be measured with postoperative diffusion-weighted magnetic resonance imaging (DW-MRI) during the first postoperative week. To our knowledge, this is the first study to explore the impact of cerebral ischemia on cognitive training for patients who have undergone cardiac surgery.

## Methods

### Study design and enrollment

This study is a multicenter, randomized controlled trial conducted at the department of cardiac surgery of the Kerckhoff Heart and Thorax Center in Bad Nauheim, Germany, and at the department of cardiovascular surgery of the University Hospital Giessen, Germany. It complies with the Declaration of Helsinki and has been approved by the ethics committee of the Justus Liebig University Giessen (ref. 28/14). The study coordinator receives information about planned elective cardiac surgery from the participating study centers, which he screens according to eligibility criteria. Potential patients will be contacted and informed verbally and in writing in detail about the purpose, procedure, and possible consequences of the study project. If the patient agrees to participate, a written informed consent form will be signed by the patient and the investigator prior to the patient’s enrollment.

Our study team consists of members of the departments of neurology, neuropsychology, neuroradiology, heart surgery, and rehabilitation who are responsible for running the study, including preparing the protocol, monitoring the study and writing the study reports. The study protocol follows the SPIRIT (Standard Protocol Items: Recommendations for Interventional Trials) guideline (see Additional file 1).

Due to the planned small sample size, the expected lack of harm and the relatively short execution time of the cognitive training (3 weeks), the implementation of a data monitoring committee was not considered.

All patients will pass a detailed neuropsychological assessment the day before surgery, at discharge from rehabilitation, and at 3 and 12 months after discharge. At every time point, patients will complete a standardized questionnaire on depression and anxiety. Questions about cognitive failure in daily life and HQL will be assessed before heart surgery and at 3 and 12 months after discharge from rehabilitation. Before surgery, data documentation will include age, sex, education, body mass index, preexisting conditions, and medication. Documentation of perioperative date will be the type and amount of anesthesia administered, duration of anesthesia administration, type and amount of analgesia administered, duration of analgesia administration, duration of surgery, duration of extracorporeal circulation, cross-clamp time and perioperative complications. Post-surgery intensive care unit (ICU) days, total length of inpatient stay, postoperative complications and postoperative delirium will be recorded. At 6–10 days after surgery, MRI of the brain will be conducted to screen for cerebral ischemia, hemorrhage, or other acute pathologic conditions potentially confounding neuropsychological assessment and the effects of cognitive training. Following the inpatient stay in the acute hospital (approximately 7 days), patients will be directly transferred to the department of rehabilitation at the Kerckhoff Clinic in Bad Nauheim, Germany.

During their stay at the rehabilitation center, which usually lasts 3 weeks, all patients will receive standard cardiac rehabilitation including physical exercise, medical management and nutritional counseling. The cognitive training group will undergo an additional cognitive training program consisting of paper-and-pencil exercises. The study design is shown in Fig. 1. A detailed trial schedule in accordance with the Standard Protocol Items: Recommendation for Interventional Trials (SPIRIT) guideline is shown in Table 1.

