### Randomization

After enrollment and a baseline assessment, patients will randomly be assigned by the study coordinator to the cognitive training group or the control group, which will not receive cognitive training. Patients will be randomized using a computer-generated randomization list with a 1:1 blocked allocation ratio. The randomization list will be sequentially numbered and will be generated by the study coordinator prior to the start of the study.

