### Planned statistical analyses

The effect of cognitive training will be analyzed by repeated measures (mixed between-within) analysis of variance (ANOVA) with groups (control group/intervention group) as the between-subject factor and assessment time (baseline and all follow-up assessments) as the within-subject factor for all cognitive tests and questionnaires, respectively. Assumptions for repeated measures ANOVA will be tested using the Levene test for variance-homogeneity and Mauchly’s test for sphericity. If sphericity is violated, alpha levels will be adjusted using the Greenhouse-Geisser correction. Normal distribution will be tested using the Shapiro-Wilk test. To control for the possibility of confounder variables that could affect the results, we will conduct additional repeated measures analysis of covariance (ANCOVA), which includes covariates such as preoperative cognitive values, age, sex, education, psychiatric scores (depression/anxiety), and perioperative variables such as duration of extracorporeal circulation, administration of anesthesia, and number and size of ischemic lesions.

Post hoc explorative between-subject comparisons will be analyzed using the *t* test for independent samples. In this case, we will compare the intervention group with the control group by calculating a change score in cognitive values (post-training score minus pre-training score). The change in cognitive values is the dependent variable, and the treatment group (cognitive training group/control group) is the independent variable.

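### Patients come from two surgical departments, but the main ANOVA has no centre term, so any centre difference in cognitive change stays in the error: a small loss of precision, without bias

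*Protocol article*

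**What the plan says.** Under Study design and enrollment, the protocol article states: "This study is a multicenter, randomized controlled trial conducted at the department of cardiac surgery of the Kerckhoff Heart and Thorax Center", continuing "and at the department of cardiovascular surgery of the University Hospital Giessen, Germany". After the acute stay there is one destination for everyone: "patients will be directly transferred to the department of rehabilitation at the Kerckhoff Clinic in Bad Nauheim".

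Under Randomization: "Patients will be randomized using a computer-generated randomization list with a 1:1 blocked allocation ratio". The same section adds: "The randomization list will be sequentially numbered and will be generated by the study coordinator prior to the start of the study". No stratification factor is mentioned.

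Under Planned statistical analyses, the main model for every cognitive test and questionnaire is a mixed repeated measures ANOVA "with groups (control group/intervention group) as the between-subject factor and assessment time" as the within-subject factor. An additional ANCOVA is to include "covariates such as preoperative cognitive values, age, sex, education, psychiatric scores (depression/anxiety), and perioperative variables such as duration of extracorporeal circulation", together with anaesthesia and the number and size of ischaemic lesions. Centre is not among the covariates named. That list is introduced by words that leave it open, but it belongs to the additional model and not to the main one.

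**The concern.** Baseline testing is the day before surgery, and the primary outcome is read at discharge from rehabilitation. The change that is analysed therefore covers the operation, the anaesthesia and the acute stay, and two departments deliver these. The article itself treats anaesthesia, bypass and embolization as possible causes of cognitive injury (Background), and it treats several perioperative variables as possible confounders (Planned statistical analyses). If the two departments differ in mean cognitive change, a model with group alone between subjects counts that difference as unexplained variation. The training effect is then estimated less precisely than the data allow.

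Centre is fixed before allocation, whether patients are randomized after the baseline assessment (Randomization) or after transfer to rehabilitation (legend of Fig. 1). Adjusting for it therefore cannot distort the comparison.

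**Working it through.** **Inputs from the article (Power and sample size estimation).** η² = 0.10, 80% power, two-sided 0.05, 37 per group, 20% dropout in each of three intervals, 72 per group recruited.

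**Inputs assumed, because the documents give neither.** Share of patients from one centre p = 0.5 (0.7 as a check), and centre gap in mean change δ = 0.2 to 0.5 within-centre SD.

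**1. The plan's own figure.**
- f = √(0.10/0.90) = 0.333, so d = 2f = 0.667.
- Two-sample t test with the noncentral t distribution: power is 79.7% at 36 per group and 80.8% at 37. The stated 37 is reproduced.
- Dropout: 37/0.8³ = 72.3, in line with the stated 72. Expected at discharge: 72 × 0.8 = 57.6, about 58 per group.

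**2. Error variance without a centre term.** In units of the within-centre variance it is 1 + p(1−p)δ². With p = 0.5:
- δ = 0.2: 1 + 0.25 × 0.04 = 1.010, or 1% more.
- δ = 0.3: 1 + 0.25 × 0.09 = 1.0225, or about 2% more.
- δ = 0.5: 1 + 0.25 × 0.25 = 1.0625, or about 6% more.

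**3. Power.** The unadjusted analysis works with d/√(1 + p(1−p)δ²), and the adjusted analysis with d = 0.667. The one between-subject degree of freedom spent on centre is ignored, as it is negligible here.

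| Per group | δ | Without centre | With centre | Loss (points) |
|---|---|---|---|---|
| 37 | 0.2 | 80.4% | 80.8% | 0.4 |
| 37 | 0.3 | 79.9% | 80.8% | 0.9 |
| 37 | 0.5 | 78.4% | 80.8% | 2.4 |
| 58 (discharge) | 0.2 | 94.3% | 94.5% | 0.2 |
| 58 (discharge) | 0.5 | 93.2% | 94.5% | 1.3 |

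A 70:30 split gives slightly smaller losses. For δ = 0.5 the variance rises by 0.21 × 0.25 = 5.25%, and power at 37 per group is 78.7%. If d = 0.667 is instead taken in units of the total SD, with p = 0.5 and the 0.5 gap in the same units, adding centre raises power at 37 per group from 80.8% to 83.2%, again 2.4 points.

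**4. Chance imbalance is not a second cost.** The unadjusted variance of the difference between arms is

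2(1 + p(1−p)δ²)/n = 2/n + 2p(1−p)δ²/n.

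The second term is exactly the variance of the shift that chance differences in centre mix produce. With n = 58, p = 0.5 and δ = 0.5:
- 2/58 = 0.0345, a standard error of 0.186;
- 2 × 0.0625/58 = 0.00216, an SD of the shift of 0.046;
- sum 0.0366, a standard error of 0.191.

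The unadjusted standard error of 0.191 already contains the imbalance.

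**The case against.** The strongest reply is that whether centre enters the model is a detail for the full protocol or the analysis plan, and that the open covariate list does not exclude it. This stands only for the additional ANCOVA. The article does fix the between-subject structure of the main model, and adding centre to a supplementary analysis would not change the main result.

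A second reply is that training and rehabilitation take place in one department, so the usual reason for a centre term, delivery that differs by site, is largely absent. This is right about the intervention. It does not remove differences in surgery, anaesthesia and acute care between baseline and discharge.

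Third, the additional ANCOVA adjusts at patient level for bypass time, anaesthesia and lesions, which may absorb part of a centre effect. Using change from baseline also removes centre differences in starting level. Both are true, and both make the likely gain smaller. The first applies only in the additional model.

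A reader might also infer more than the text supports:
- **That one unstratified list certainly serves both centres.** The article speaks of a list in the singular and is silent on stratification, so this is an inference. It does not rule stratification out.
- **That only Giessen patients change hospital before rehabilitation.** The article says only that patients are transferred directly.

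**Conclusion.** The point holds as a minor one. The main model leaves any centre difference in cognitive change in the error, and the cost is precision alone: about 1% to 6% more error variance and about 0.4 to 2.4 points of power at 37 per group. At discharge, with about 58 per group, the loss is about 1.3 points for a 0.5 SD gap. These figures rest on an assumed even split and an assumed gap of 0.2 to 0.5 SD. If the departments do not differ in mean change, nothing is lost.

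A reader might conclude that the omission biases the training effect or raises the false-positive rate. It does neither: allocation is random, and the unadjusted standard error covers imbalance in centre mix. A reader might also point to a possible shift of 1.96 × √(2 × 0.25/58) × 0.5 = 0.091 SD, which is 0.091/0.667, about 14% of the design effect. That figure combines an even split, the largest assumed gap and an imbalance at its 95% limit. It is a stacked worst case from assumed inputs, and it describes the same variance already counted above.

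The stated sample size needs no change.

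**What to change.** In Planned statistical analyses, add surgical centre (two levels) to the main training-effect model for each cognitive test and questionnaire, as a main effect with its centre-by-time term. State that no group-by-centre terms are included, because a default factorial ANOVA would add them. Keep centre in the additional ANCOVA as well.

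The centre-by-time term is needed because the training effect is the group-by-time interaction. A centre main effect alone removes only differences in average level and leaves differences in change untouched.

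The cost is one degree of freedom between subjects plus one for each within-subject time contrast, so 1 + 3 with four time points. No new data are needed, since each patient's surgical department is known, and the sample size stays as it is. The change concerns analysis only, so it can be made while recruitment continues. It should be recorded before outcomes are compared between the arms, so that adjustment for centre does not become a later discretionary choice.

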**Fig. 1 Fig1:**
[figure not shown]
Timeline of study-related events. The first assessment includes neuropsychological tests and questionnaires on the day before surgery. Within 6–10 days after surgery, magnetic resonance imaging (MRI) of the brain is scheduled. After the acute hospitalization, patients will be transferred to the center of rehabilitation and randomly assigned to the cognitive training group or the control group. A second neuropsychological assessment will be administered at discharge from rehabilitation. To determine the long-term effects of the cognitive training, a neuropsychological test and questionnaires will be administered at 3 and 12 months after discharge from rehabilitation

**Table 1 Tab1:**
[figure not shown]
Trial schedule of enrollment, interventions, and assessments

*MRI* magnetic resonance imaging, *TMT* Trail Making Test, *AKT Alterskonzentrationstest*, *VLMT Verbaler Lern- und Merkfähigkeitstest*, *NVLT* Non-Verbal Learning Test, *SKT Syndrom-Kurztest*, *RWT Regensburger Wortflüssigkeits-Test*, *SVT Symbolverarbeitungstest*, *HADS* Hospital Anxiety and Depression Scale, *s-CFQ* Cognitive Failure Questionnaire for self-assessment, *f-CFQ* Cognitive Failure Questionnaire for foreign assessment, *SF36* Short Form-36

### Inclusion and exclusion criteria

Patients receiving elective aortic or mitral valve replacement/reconstruction with or without CABG will be included in this study. All heart operations will be performed with standard extracorporeal circulation. Due to the use of a standardized psychological assessment, patients must be native German speakers. Exclusion criteria are history of stroke and preexisting psychiatric or neurological disorders. Patients whose health insurance does not grant the postoperative treatment in the department of rehabilitation at the Kerckhoff Clinic in Bad Nauheim (Germany) must also be excluded.

If patients no longer wish to participate in the cognitive training or neuropsychological examination due to a deteriorating state of health, lack of motivation, any other reason, or without reasons given, they may discontinue participation in the study. Furthermore, participants will be excluded from the study if they are transferred to another clinic during their stay in the rehabilitation center.

Medical and psychological interventions in the context of other studies that may exert effects on patients’ cognition are prohibited. In general, concomitant care and interventions as part of the standard rehabilitation program are permitted.

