Within-subject comparisons will be analyzed using the paired *t* test. When the assumptions for parametric tests (normal distribution, variance-homogeneity between two groups) are not given, the variables will be analyzed using non-parametric variance techniques. In this case, between-group differences will be calculated using the Mann-Whitney U test, using change scores in cognitive values (post-training score minus pre-training score) and the Wilcoxon signed-rank test for within-group comparisons. Nominal variables will be analyzed by Pearson’s chi-squared test. Depending on the parametric level of the data, correlation with continuous variables will be calculated using Pearson product-moment correlation, Spearman rank correlation, or Kendall tau correlation. Effect size of the cognitive training will be calculated by the difference in the pretest-posttest measure between the intervention and control group, weighted by the pooled standard deviation of the pretest measurement, because this is the recommended choice for a pretest-posttest controlled design [38]. The criterion for statistical significance will be set at *p* < 0.05. In the case of multiple tests, we will control *p* values using the false discovery rate (FDR) correction method [39]. Since we expect dropout of some patients on follow-up assessments, all patients will be included in the intention-to-treat analysis, where missing data will be imputed by a multiple imputation method. To evaluate the impact of missing data, a complete case analysis will also be performed, followed by best-worst and worst-best case sensitivity analyses.

Another approach to identifying a training effect on cognition will be to compare the frequencies of POCD and POCI between the groups using Pearson’s chi-squared test. POCD will be defined as a decline from pre to post assessment of 1 standard deviation in at least two neuropsychological parameters as this is a widely used method [2]. Similarly, POCI will be defined as an improvement from pre to post assessment of 1 standard deviation in at least two neuropsychological parameters.

Interim analyses will be carried out during the study period to identify adverse events, an overwhelming effect, or the futility of the experimental arm. In this case, the study could be terminated prior to its completion. The decision will be made by the study team.

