### Power and sample size estimation

Cognitive training for patients undergoing heart surgery administered by de Tournay-Jette et al. (2012) [19] revealed medium-to-large effect sizes (*η*^2^ = 0.10–0.23). We have decided to use the smaller effect size (*η*^2^ = 0.10) for calculation so as not to underestimate the required sample size. Using this effect size, 37 patients per group are needed to obtain statistical power of 80% at a significance level of *p* = 0.05 (two-tailed). Based on previous cardiosurgical studies, we estimate a dropout rate of 20% between each of the four assessment time points. Thus, the number of study patients recruited at baseline assessment was fixed at 72 patients per group. For sample size and statistical power calculations, we used G*Power-3 analysis software.

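### Excluding patients who are transferred during rehabilitation conflicts with the promised intention-to-treat analysis, and no route is stated for stopping training while staying in follow-up

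*Protocol article*

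**What the plan says.** Four parts of the protocol article bear on this point.

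- **Inclusion and exclusion criteria, transfer.** The rule is mandatory: "participants will be excluded from the study if they are transferred to another clinic during their stay in the rehabilitation center".
- **Inclusion and exclusion criteria, withdrawal.** One sentence covers training and testing together. It begins "If patients no longer wish to participate in the cognitive training or neuropsychological examination due to a deteriorating state of health, lack of motivation", allows any other reason or none, and ends "they may discontinue participation in the study".
- **Timing of randomization.** The Randomization section says "After enrollment and a baseline assessment, patients will randomly be assigned by the study coordinator". The legend of Fig. 1 places allocation on arrival in rehabilitation: "patients will be transferred to the center of rehabilitation and randomly assigned to the cognitive training group or the control group".
- **Planned statistical analyses.** Dropout is expected, and "all patients will be included in the intention-to-treat analysis, where missing data will be imputed by a multiple imputation method". A complete-case analysis and best-worst and worst-best analyses follow as sensitivity checks.

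The primary outcome is measured at discharge from rehabilitation (Primary outcome measure). The control group receives neither training nor placebo (Abstract, Methods).

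**The concern.** Exclusion for an event after randomization is what intention to treat is meant to prevent. The transfer rule covers the period that ends with the primary assessment, so a transferred patient would have no cognitive score after baseline. If exclusion also ends follow-up, the 3- and 12-month scores are lost too. A move to another clinic during rehabilitation plausibly reflects a worse clinical course, so these losses are unlikely to be random.

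The withdrawal sentence raises a related but weaker issue. It does not separate giving up the training from giving up the assessments. A patient in the training arm who is tired of the exercises but willing to be tested has no stated way to remain. Controls have no training to stop, so this route out exists in one arm only.

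At stake are who is counted in the primary comparison and whether outcomes that could have been obtained are obtained.

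**Working it through.** **1. Is the exclusion after randomization?** Randomization is after the baseline assessment according to the Randomization section, and on arrival in rehabilitation according to the Fig. 1 legend. A transfer during the rehabilitation stay comes later than either point. The exclusion is therefore post-randomization on any reading.

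**2. Are the two rules reconciled?** One section removes the transferred patient from the study; the other includes all patients in the analysis. The article does not say whether an excluded patient remains in the intention-to-treat set, is imputed, or is invited to later visits.

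**3. The plan's own figures (Power and sample size estimation).**
- Effect: η² = 0.10, so f = √(0.10/0.90) = 0.333 and d = 2f = 0.667.
- A two-sample t test with two-sided alpha 0.05 has 79.7% power at 36 per group and 80.8% at 37. The stated 37 is reproduced.
- Dropout of 20% over three intervals: 37/0.8³ = 72.3, against the stated 72. Reproduced within rounding.

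**4. How many patients lack the primary outcome under the plan's 20%?** 72 × 0.8 = 57.6 per group are assessed at discharge. About 14 per group, or 29 of 144, are missing. Power at 57 per group for d = 0.667 is about 94%, so the issue is bias and not power. The document does not say how many of these losses would be transfers or patients who stopped training.

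**5. Illustration of bias.** Suppose that patients lost would have scored k SD below completers in the same arm, on the change scale that the plan compares. In a completers-only comparison, each arm's mean is then too high by k × (share lost). With equal k in both arms:

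bias in favor of training = k × (share lost in training − share lost in control)

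| Loss, training / control | k = 0.3 | k = 0.5 | k = 0.8 |
|---|---|---|---|
| 20% / 20% (the plan's rate in both arms) | 0 | 0 | 0 |
| 25% / 15% (assumed) | 0.03 | 0.05 | 0.08 |
| 30% / 10% (assumed) | 0.06 | 0.10 | 0.16 |

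All values of k and both unequal splits are assumptions; the document gives none of them. Against the planned d of 0.667, the last row is 9% to 24% (0.06/0.667 and 0.16/0.667).

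**The case against.** The strongest reply is that exclusion from the study may mean only that participation ends, with the missing scores then imputed. The sentence on intention to treat is introduced by the expectation of dropout, so this reading is possible, and under it the conflict over the analysis set disappears. The article does not say so, however. Even on this reading, the rule ends data collection for patients who might still have been tested.

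Several other objections stand and limit the point.

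- The transfer rule applies to both arms. A reader might infer that it removes patients mainly from the training arm, but nothing in the document supports that.
- The withdrawal sentence permits leaving and does not require it. Voluntary withdrawal is compatible with an imputed intention-to-treat analysis, so it is not a second contradiction.
- The main analysis is imputed, and imputation can condition on baseline scores and covariates. The best-worst and worst-best analyses probe the case in which missing training-arm patients did badly. These are real safeguards. They show how sensitive the result is, but they do not define the analysis set or replace observed scores.
- A reader might take the two statements on the timing of randomization as contradictory. They are compatible: baseline before surgery, allocation later. The statement that "the number of study patients recruited at baseline assessment was fixed at 72 patients per group" is loose wording, because groups need not exist at that time, but it reads naturally as a recruitment target.

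**Conclusion.** The point holds in a limited form. A mandatory exclusion after randomization and a promise to analyze all patients stand side by side unreconciled, and the exclusion falls in the window just before the primary assessment. In addition, leaving the study is the only stated outcome for a patient who no longer wants the training. Since only the training arm can meet that condition, this is a possible route to unequal dropout, not a documented imbalance.

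The document does not support a figure for the bias. A reader might apply the plan's 20% dropout to the training arm alone, assume a shortfall of 1 SD, and arrive at 0.20 SD, or 30% of the planned effect. That would require no loss at all among controls, whereas the plan applies its 20% to both arms, and equal loss with equal shortfall gives no bias in the completer difference. The range of 0.06 to 0.16 SD rests on an assumed 30% versus 10% split and an assumed shortfall of 0.3 to 0.8 SD. It describes a completers-only comparison, which the plan uses only as a sensitivity analysis. The sample-size figures are unaffected.

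**What to change.** Replace the transfer exclusion with wording to this effect:

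- Every randomized patient remains in the intention-to-treat set, whatever happens during rehabilitation.
- Patients who are transferred, or who stop the training, are still invited to the remaining assessments: at least those at 3 and 12 months, and the discharge assessment where feasible. The only exception is withdrawal of consent for assessment.
- Stopping the training and withdrawing from the study are recorded as separate events, each with its reason.

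This changes follow-up and analysis only, not care. The cost is the rewording and a few extra assessments. The discharge assessment is the harder one: a transferred patient has no ordinary discharge visit at this center, and a full battery by a blinded neuropsychologist would have to be arranged elsewhere or at another time. Recruitment began in July 2016 and was expected to end in February 2020, so outcomes of patients already excluded may not be recoverable. Those patients should still be counted in the analysis set and reported by arm.
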